#### Specific measures used in online assessments

The PHQ-9 will be used to measure depression symptomatology [50]. The PHQ-9 is a reliable and valid nine-item measure of depression severity over the past 2 weeks [44, 51]. Each of the nine items of the PHQ-9 is scored as 0 (not at all), 1 (several days), 2 (more than half the days), or 3 (nearly every day). Scores are summed to provide a total score (score range 0–27 with 0 indicating no depressive symptoms and 27 indicating all symptoms occurring nearly daily). The criterion and construct validity of the PHQ-9 has previously been demonstrated, with 73% sensitivity and 98% specificity in detecting major depression compared to clinician-based assessment [28, 50] and, regardless of diagnostic status, typically represents clinically significant depression [50]. The measure has excellent internal consistency (Cronbach *α* > 0.85 in multiple samples) and test-retest reliability (α = 0.84) [52].

Anxiety will be measured using the 2-item Generalised Anxiety Disorder scale (GAD-2) [47]. The GAD-2 consists of the two core criteria for generalized anxiety disorder, which have been shown to be effective screening items for panic, social anxiety, and post-traumatic stress disorders [47]. The GAD-2 begins with the stem question: “Over the last 2 weeks, how often have you been bothered by the following problems?” Response options are “not at all”, “several days”, “more than half the days”, and “nearly every day”, scored as 0, 1, 2, and 3, respectively (total ranging from 0 to 6). A total scale score ≥ 3 is suggested as a cut-off point between the normal range and “probable anxiety” [47].

Resilience will be measured by the 10 item Connor-Davidson Resilience Scale (CD-RISC-10) [53]. The CD-RISC-10 is a self-rated measure, with each question rated on a 5-point scale from 0 (‘not true at all’) to 4 (‘true nearly all the time’). The CD-RISC-10 has been shown to differentiate between individuals who function well after adversity and those who do not and measures the core features of resilience and the ability to tolerate experiences [53]. It is believed that increased resilience may reduce rates of mental ill health [54].The scale demonstrates high internal consistency (Cronbach’s α = 0.89), construct validity, and test-retest reliability in the general population and in clinical settings [48]. Total scores range from 0 to 40 with higher scores corresponding to greater resilience. The scale has been shown to have good concurrent validity, with higher resilience on the scale associated with lower levels of perceived stress [48] Validity is high relative to other measures and reflects differentiation in resilience among diverse populations, showing that higher levels of resilience are consistent with lower levels of perceived stress vulnerability [48].

Wellbeing will be assessed using the 5-item WHO Wellbeing Index (WHO-5) [45, 46]. Participants are asked to self-report on the presence or absence of wellbeing on a 6-point scale ranging from 5 (‘all of the time’) to 0 (‘none of the time.’) Raw scores range from 0 to 25 where 0 indicates the worst possible quality of life while a score of 25 represents the best possible quality of life. A score ≤ 13 or an answer of 0 or 1 on any of the five items shows poor wellbeing. WHO-5 is a psychometrically sound measure of well-being with high internal consistency (Cronbach’s α = 0.84) and convergent associations with other measures of well-being [55].

Work Performance will be measured using three items (performance items A10, A11, A12) from the Health and Work Performance Questionnaire (HPQ) [49]) and two additional items pertaining to: i) sickness absence over the past month (days absent more generally, and days absent specifically for mental health reasons), and ii) weeklong sickness absence over the past 6-months (weeks absent more generally, and weeks absent specifically for mental health reasons).

Service use and management items comprised of seven items assessing lifetime and past month service use, along with current medication use. Participants were also asked about their abilities (perceived capability and effectiveness) to manage their mental fitness, and autonomy (choice and freedom) in management. These were scored on a 7-point Likert scale from strongly disagree to strongly agree.

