### Random allocation

Randomisation will occur immediately following completion of the baseline assessment using automated procedures integrated into the trial management software. The algorithm for randomisation will consist of a block design, stratified by industry type, with a block size of 10.

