### Assessment

#### Administration of assessments

Assessments will be completed at baseline, post-intervention (5-weeks), and 3-month follow-up. Baseline assessment includes outcome measures pertaining to depression symptomatology (Patient Health Questionnaire (PHQ-9) [44]), wellbeing (World Health Organisation-5 (WHO-5) Well-Being Index [45, 46]), anxiety symptomatology (General Anxiety Disorder-2 item (GAD-2) [47], resilience (Connor-Davidson Resilience Scale 10-item (CD-RISC10) [48]), work performance and absenteeism (Health and Work Performance Questionnaire (HPQ) [49]). In addition to these measures, demographic and service use information will be collected. The application monitors usage data including number of log-ins, frequency of use, time spent in-app, and activity completion rates. This data will be used to examine program engagement.

Post-intervention assessment will occur at 5 weeks’ post-baseline, to allow users extra time to complete the 30-day program. Participants will be reminded to complete the post-intervention assessment via text messages to phone numbers provided in order to address for the possibility that users may delete the app during the trial. Participants will complete an online questionnaire similar to the baseline measure (see Table 1), and again at 3 months post-baseline (“3-month follow-up”). Participants will receive up to three text messages and a call at each follow-up assessment time point, linking them to an online platform through which they can complete the assessment. On completion of each assessment, participants will be entered into a draw to win one of four $200 Visa gift cards.

**Table 1 Tab1:** Assessment measures

	Baseline	Post-intervention	3-month follow-up
Demographics	×		
Patient Health Questionnaire-9 item (PHQ-9) [44]	×	×	×
General Anxiety Disorder-2 item (GAD-2) [47]	×	×	×
World Health Organisation-5 (WHO-5) Well-Being Index [45, 46]	×	×	×
Connor-Davidson Resilience Scale 10-item (CD-RISC10) [48]	×	×	×
Health and Work Performance Questionnaire (HPQ) [49]	×	×	×
Service utilisation and management items	×	×	×
Program feedback		×	

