#### Secondary outcomes

A range of secondary outcomes will be considered, including change in anxiety symptomatology (as measured by the PHQ-2) at both 5-week and 3-month follow up. Other secondary outcomes include incident caseness of depression at 5-week and 3-month follow-up (as measured by the PHQ-9 diagnostic algorithm), and the level of depression symptoms (PHQ-9) at 5-week follow up. Finally, change in Wellbeing (as measured by the WHO-5) and change in occupational functioning (as measured by the HPQ and sickness absence questions) at both 5-week and 3-month follow-ups will be outcomes of interest.

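### The week-long sickness absence item looks back 6 months at visits held 5 weeks and 3 months after randomisation, so much of what it counts precedes randomisation

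*Protocol article*

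**What the plan says.** All references are to the protocol article.

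- *Specific measures used in online assessments* describes two absence items alongside three HPQ performance items. One asks for days absent in the past month. The other asks for "weeklong sickness absence over the past 6-months (weeks absent more generally, and weeks absent specifically for mental health reasons".
- *Secondary outcomes* lists "change in occupational functioning (as measured by the HPQ and sickness absence questions) at both 5-week and 3-month follow-ups".
- *Administration of assessments* fixes the timing: "Post-intervention assessment will occur at 5 weeks’ post-baseline", and "again at 3 months post-baseline" for the second follow-up. On content it says: "Participants will complete an online questionnaire similar to the baseline measure". Table 1 shows the HPQ at all three assessments and does not list the absence items separately.
- *Random allocation*: "Randomisation will occur immediately following completion of the baseline assessment".
- *Analysis plan* treats scaled secondary measures like the primary outcome, testing whether change differs by arm.

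The article gives one description of the absence items for all assessments. It neither states a shorter recall period at follow-up nor confines the 6-month item to baseline.

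**The concern.** The look-back is longer than the whole follow-up, so at both visits it must reach back before randomisation. Absence from that time is history that the app cannot alter, and the same weeks have already been counted in the baseline answer.

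This has three consequences. A percentage reduction computed on the reported count understates the true one. Pre-randomisation absence adds variance without adding information about treatment. And change is not a plain before-and-after contrast: with perfect recall it compares the newest 5 weeks (or 3 months) with the oldest 5 weeks (or 3 months) of the baseline window. Participants must also remember the overlapping weeks the same way twice for them to cancel.

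At stake is the reading of one occupational result. The Discussion motivates the trial partly by absenteeism and presents the assessment of occupational outcomes as one of its distinctive features, so a null or small effect on week-long absence would attract comment.

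**Working it through.** The article states no power, event or sample-size figure for absence, so there is no figure of the plan's own to reproduce.

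**Inputs from the article.** Look-back W = 6 months = 26.1 weeks. Follow-up times w = 5 weeks and 3 months (13.0 weeks). Baseline time equals randomisation time.

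**Assumptions added here.** A constant absence rate λ per week; independent Poisson absence weeks; accurate recall. For illustration, λ = 0.02 absence weeks per week and a true reduction of 30%.

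**1. Share of the window after randomisation, f = w/W**
- 5 weeks: 5/26.1 = 0.19, so 81% is before randomisation.
- 3 months: 3/6 = 0.50, so 50% is before randomisation.

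**2. Relative effect on the reported count = f × true relative effect**
- 5 weeks: 0.19 × 30% = about 6% (5.7%).
- 3 months: 0.50 × 30% = 15%.
- For true reductions of 10% and 50%, the reported reductions are 1.9% and 9.6% at 5 weeks, and 5% and 25% at 3 months.

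**3. Absolute difference between arms = λ × w × reduction, whichever window is used**
- 5 weeks: 0.02 × 5 × 0.30 = 0.03 weeks.
- 3 months: 0.02 × 13 × 0.30 = 0.08 weeks.

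Pre-randomisation weeks have the same expectation in both arms, so they do not move this difference.

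**4. Sample needed, relative to an item limited to time since randomisation**

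The absolute difference is the same, so the ratio of sample sizes is the ratio of variances. The limited item has variance λw.

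| Analysis of the 6-month item | Variance | Ratio to λw | 5 weeks | 3 months |
|---|---|---|---|---|
| Follow-up count, baseline ignored | λW | 1/f | 5.2 | 2.0 |
| Change from baseline | λw + λw | 2 | 2.0 | 2.0 |
| Adjusted for baseline | λW[1 − (1 − f)²] = λw(2 − f) | 2 − f | 1.8 | 1.5 |

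In the change score the shared W − w weeks cancel, leaving two separate stretches of length w. In the adjusted analysis the correlation between the baseline and follow-up counts is (W − w)/W = 1 − f.

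**5. Simulation check** (rate 0.02, 30% reduction). With baseline ignored, the standardised effect fell to 0.42 (5 weeks) and 0.69 (3 months) of its value for the limited item, against √f = 0.44 and 0.71 from the formula. When absence rates varied between people the figures were 0.34 and 0.61. With baseline as covariate for the limited item, the sample ratios were 1.8 to 2.1 for change scores and 1.5 to 1.9 for the baseline-adjusted 6-month item, with or without such variation.

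**6. The other absence item.** A month is about 4.3 weeks, less than 5, so the past-month window lies wholly after randomisation at both visits.

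**The case against.** The strongest reply is that the planned quantity is change. With accurate recall the overlapping weeks appear in both answers and drop out, so the expected difference between arms in weeks absent is the full post-randomisation effect. This stands. A reader might infer that the outcome is simply biased towards no difference. The documents do not support that for the absolute difference; it holds only for relative effects on the 26-week count. What remains for the absolute difference is extra noise, and recall error that stops the overlap from cancelling exactly.

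A reader might also square the shares and conclude that 1/0.19² = 27 times and 1/0.5² = 4 times the sample is needed. That compares the item with a 26-week window lying wholly after randomisation, at equal noise. The last visit is at 3 months, so neither this trial nor any reworded item could supply such a window. The fair comparator is an item limited to time since randomisation.

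It can further be said that follow-up content is described as similar, not identical, and that the questionnaire itself is not shown. This also stands: the unchanged window is read from three sections together. Nothing in the article contradicts it.

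Finally, occupational functioning is a secondary outcome and the past-month item is already collected, so a null on this item would not leave absence untested. That is correct and limits the weight of the point.

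**Conclusion.** The point holds for one of the two absence items within a secondary outcome. As described, only 19% of its window at 5 weeks and 50% at 3 months can reflect the app. Relative effects are diluted to those shares. The absolute difference is not biased under accurate recall but is estimated less efficiently: about 2 times the sample for change scores, 1.8 and 1.5 times with baseline adjustment, and 5.2 and 2 times only if baseline is ignored.

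The shares rest on the article's own timings and on the inference that the recall window is the same at follow-up. The dilution figures also need a constant absence rate, and the sample ratios need independent Poisson absence weeks and accurate recall.

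It would go too far to call this a failure of a main aim. The stated aim is to treat depressive symptoms. The PHQ-9 primary outcome and the past-month absence item are unaffected. It is a cheap improvement worth making.

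**What to change.** Either of two changes would do.

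1. Keep the 6-month item at baseline as a descriptor and covariate. At follow-up, ask about week-long absence since baseline and analyse it as a rate per week of exposure.
2. Drop the 6-month item as a follow-up outcome and name past-month days absent as the absence outcome.

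The first means rewording one online item, plus two statistical costs. Week-long absence will be sparse at 5 weeks: at the illustrative rate of 0.02, about 0.02 × 5 = 0.1 absence weeks per person. And the baseline and follow-up windows (26, 5 and 13 weeks) differ, so a simple change-from-baseline model no longer applies to this item.

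The second needs no new data, but it measures days rather than week-long absence, and at 3 months it covers only the latest 4.3 of the 13 weeks since randomisation.

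If the follow-up questionnaire already uses a shorter window, stating that in the article settles the matter.

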#### Safety protocol

In any trial concerned with mental health, there is the potential for participants to experience psychological distress. Those who meet criteria for the trial will within the app trigger the user to be directed to a “get support” page (at each assessment point) and will suggest the participant seek further help from these support services or their general practitioner (GP). Additionally, an optional call-back service for individuals requiring further support or direction is provided. This call-back will be conducted by a team-member with psychology training, within 4 days, with the purpose to guide participants into necessary care arrangements. If the team member still has concerns for the participant’s safety, an accredited psychiatrist will contact the participants within the next 24 working hours. Participants will also receive an SMS with a range of support service contacts, and another reminder to consult with their GP regarding their mental health.

#### Study hypotheses and outcomes

We hypothesise that participants receiving the *HeadGear* intervention will have reduced levels of depression symptomatology at post-intervention and 3-month follow-up, compared to participants in the attention-matched control condition. While the primary analyses will be conducted on the entire sample (to examine the intervention effect). We also predict the intervention effect to vary according to the level of depression symptoms at baseline [56], with a greater effect amongst those with higher levels of symptomatology.

Secondly, it is hypothesized that—relative to the control group—*HeadGear* Intervention participants will have lower rates of depressive disorder as detected by the PHQ algorithm at all follow-up time points. We also hypothesise that the intervention group will have reduced levels of anxiety symptomatology, and improved wellbeing, resilience, and work performance, at all follow-up time points, relative to controls.

#### Primary outcome

The primary outcome measure of the study will be the level of depressive symptomatology (as measured by the PHQ-9) at the 3-month follow up period.

#### Secondary outcomes

A range of secondary outcomes will be considered, including change in anxiety symptomatology (as measured by the PHQ-2) at both 5-week and 3-month follow up. Other secondary outcomes include incident caseness of depression at 5-week and 3-month follow-up (as measured by the PHQ-9 diagnostic algorithm), and the level of depression symptoms (PHQ-9) at 5-week follow up. Finally, change in Wellbeing (as measured by the WHO-5) and change in occupational functioning (as measured by the HPQ and sickness absence questions) at both 5-week and 3-month follow-ups will be outcomes of interest.

### Statistical analysis

#### Analysis plan

Primary analyses will be undertaken on an intent-to-treat basis, including all participants as randomised, regardless of treatment received or withdrawal from the study. Likelihood based methods (mixed-model repeated measures (MMRM)) methods will be favoured to analyse change in the primary outcome measure (PHQ-9). A priori planned comparisons of change from baseline across the 3-month follow up period will be used to test the primary hypothesis. An unstructured variance-covariance matrix will be used to accommodate relationships between observations at different occasions. Variables found to be substantially imbalanced between groups post randomisation will be tentatively included in these models and retained if statistically significant and influential on outcomes. Similar analyses of scaled secondary measures will assess differential change due to intervention arm. Mathematical transformation or categorisation of raw scores may be undertaken to meet distributional assumptions and address any violation of assumptions attributable to outliers.

Baseline characteristics will be used to define subgroups that would be the targeted if the app were offered as treatment. Group membership will be used for models to evaluate moderation of effectiveness by adding appropriate interaction terms and undertaking planned comparisons. The effect on outcome of level of baseline depressive symptom levels, level of functional improvement and recruitment method at baseline will be explored using an analysis of covariance approach using baseline measures as a covariate and including a covariate by intervention arm interaction term in models. The effectiveness of the active intervention at clinically relevant levels of baseline covariates will be assessed using planned comparisons while the lowest values of covariates associated with a significant benefit of the intervention will be established using a Johnson and Neyman [57] approach.

All tests of treatment effects will be conducted using a two-sided alpha level of 0.05 and 95% confidence intervals.

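### The primary analysis does not fix one 3-month contrast as the deciding test, and gives baseline PHQ-9 and the industry strata no prespecified place in the model

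*Protocol article*

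**What the plan says.** Five parts of the Protocol article bear on the primary test.

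- **Primary outcome:** the "level of depressive symptomatology (as measured by the PHQ-9) at the 3-month follow up period". This is one measure at one time.
- **Secondary outcomes:** these include "the level of depression symptoms (PHQ-9) at 5-week follow up".
- **Study hypotheses and outcomes:** the lead hypothesis is that the intervention arm "will have reduced levels of depression symptomatology at post-intervention and 3-month follow-up", compared with control.
- **Analysis plan:** the method is a likelihood-based mixed model for repeated measures (MMRM), by intention to treat. "A priori planned comparisons of change from baseline across the 3-month follow up period will be used to test the primary hypothesis". On covariance: "An unstructured variance-covariance matrix will be used to accommodate relationships between observations at different occasions". On covariates: "Variables found to be substantially imbalanced between groups post randomisation will be tentatively included in these models and retained if statistically significant" and influential on the outcome. Analysis of covariance with the baseline measure appears in the next paragraph, for the moderation models only. Every treatment test is two-sided at 0.05.
- **Random allocation:** blocks are "stratified by industry type, with a block size of 10". The primary model does not mention industry.

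**The concern.** The sentence that defines the confirmatory test does not pick out one number. Plural comparisons of change across the period could mean the baseline-to-3-month contrast, a contrast at each of the two visits, or an average over visits. The hypothesis it serves is stated at both visits, while the outcome section names only the later one. The result that decides the trial should not depend on which reading is adopted after the data are in.

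The treatment of covariates is the second issue. Baseline PHQ-9 is normally the strongest predictor of follow-up PHQ-9, and industry is part of the randomisation design. Neither is fixed in the primary model. What is fixed is a rule that admits variables according to observed imbalance and keeps them according to their significance and influence on outcome. Under that rule the adjustment set is chosen with outcome data in view. It will also tend to miss industry, because stratification is there to balance it.

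Power is at stake, together with a primary result whose definition is open to choice. No bias in the treatment estimate from omitting these terms is alleged.

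**Working it through.** **Inputs from Sample size:** 80% power, two-sided alpha 0.05, pre-post correlation r = 0.50, 266 evaluable per group. No numeric effect size is given; the effect is called moderate.

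**The plan's own figure.** 266 per group cannot be reproduced forwards without an effect size. Solving backwards for a change-score contrast, with variance factor 2(1 − r) = 1.00:

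d = √1.00 × √(2/266) × (1.960 + 0.842) = 0.0867 × 2.802 = 0.243.

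This is an implied value, not one the plan states.

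**Change contrast against baseline-adjusted contrast** (equal SDs at baseline and follow-up):

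- Change, baseline means free by arm: 2(1 − r) = 1.00.
- Adjusted for baseline: 1 − r² = 0.75.
- Ratio: 1.00/0.75 = 1.33, which in general is 2/(1 + r). It is 1.54 at r = 0.3 and 1.18 at r = 0.7.

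Power after adjustment, starting from 80%:

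Φ(2.802/√0.75 − 1.960) = Φ(1.275) = 0.90.

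Equivalently, 80% power would need 266 × 0.75 ≈ 200 per group.

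**Check within the mixed model.** Generalised least squares with three visits, all correlations set to 0.5 (an assumption for pairs other than pre-post), complete data and 266 per group gives, for the 3-month contrast:

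| Baseline in the model | Variance factor | Power at d = 0.243 |
|---|---|---|
| Free mean in each arm | 1.00 | 80.0% |
| Common mean in both arms | 0.75 | 89.9% |

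So the loss comes from leaving baseline means free, not from using an MMRM or from expressing the effect as change.

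**Range restriction.** Entry depends on a PHQ-9 criterion, which may narrow the baseline distribution. Assume a baseline SD of 2.8, a follow-up SD of 5.4 and r = 0.26 (none of these is in the document):

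- Change: 2.8² + 5.4² − 2(0.26)(2.8)(5.4) = 29.1.
- Adjusted: 5.4² × (1 − 0.26²) = 27.2.
- Ratio of adjusted to change: 0.93, a saving of about 7%.
- Power: Φ(2.802/√0.93 − 1.960) ≈ 0.83.

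**Industry.** The document gives no between-industry variance. Assume industry explains a share q of outcome variance, with q from 1% to 5%. Leaving it out of the analysis after stratifying on it moves the effective critical value to 1.960/√(1 − q), that is 1.970 to 2.011. The true type I error is then 4.9% to 4.4%. Including industry raises 80% power to Φ(2.802/√(1 − q) − 1.960), a gain of about 0.4 to 2 points.

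**The case against.** **This is detail for the analysis plan.** How baseline and strata enter the model is often left to an SAP, and none is shown. That would answer the point if the article were silent. It is not silent: it states the contrast, states a covariate rule, and names analysis of covariance only for moderation. Still, it never says that baseline means are free by arm. An MMRM with baseline as a covariate or with a common baseline mean would not lose this power, so the power figures are conditional.

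**'Unadjusted' and 'ignores baseline'.** A reader might infer both. Neither is supported: the article allows data-driven adjustment, and a change contrast uses the baseline value, though less efficiently.

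**Change is not a different target.** Under randomisation the between-arm difference in change to 3 months has the same expectation as the difference in level at 3 months. This stands. The mismatch lies in which visit or visits decide, and the disputed sentence can be read as the baseline-to-3-month contrast.

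**Two chances at 5%.** A reader might infer that success at either visit confirms the hypothesis. The type I error would then be about 9.1% at a test correlation of 0.5 (7.0% at 0.9, 9.75% if independent). The article does not state such a rule: it lists 5-week PHQ-9 as secondary, and its hypothesis joins the visits with 'and'. The inflation is not established.

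**The 80% starting point.** The sample size came from simulation, and the model simulated is not described. The move from 80% to 90% assumes that 266 was sized for the change contrast, which cannot be shown.

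**Conclusion.** The point holds in a limited form. The hypothesis, outcome and analysis sections do not together fix one deciding contrast, although the outcome sections make the 3-month PHQ-9 the evident intention. The primary model gives neither baseline PHQ-9 nor the stratification factor a prespecified place, and it relies on covariate selection by imbalance and significance.

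If baseline means are left free by arm, which is the natural reading but is not stated, the contrast carries one third more variance than it needs at r = 0.50. Adjustment would then take 80% power to about 90%, or to about 83% under the assumed range restriction. The industry effect is small, and leaving it out errs on the conservative side. This is an avoidable loss of precision and an ambiguity worth removing. It does not threaten the validity of the trial.

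**What to change.** Replace the sentence on planned comparisons and the covariate rule with text to this effect: *The primary test is the single between-arm contrast in PHQ-9 at 3 months from the MMRM. Baseline PHQ-9 is included as a response with a common mean in both arms, and industry stratum as a fixed effect. No covariate is added to or removed from the primary model because of observed imbalance or significance. The 5-week contrast is secondary.* Align the lead hypothesis with this by marking its 3-month part as primary.

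The common-mean form is preferable to entering baseline as a covariate. It reaches the same efficiency in the complete-data calculation, and it keeps participants who have only a baseline score in the likelihood, in line with the stated intention to include everyone randomised. A model with baseline as a covariate ordinarily drops them.

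The cost is wording only. Baseline PHQ-9 is already in the assessment schedule, industry type is already needed for randomisation, and the sample size need not change.

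### The primary PHQ-9 model takes its covariates from chance imbalance and significance, so the stated 5% level and 95% coverage are not assured and power is given up

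*Protocol article*

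**What the plan says.** Under Analysis plan, the protocol article sets an intention-to-treat mixed model for repeated measures for PHQ-9, with planned comparisons of change from baseline. It then gives the rule for covariates: "Variables found to be substantially imbalanced between groups post randomisation will be tentatively included in these models and retained if statistically significant". The same sentence makes influence on the outcome a second condition for keeping a variable. The models meant are those for the primary outcome.

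The next sentence turns to the other scales: "Similar analyses of scaled secondary measures will assess differential change due to intervention arm". After it comes: "Mathematical transformation or categorisation of raw scores may be undertaken to meet distributional assumptions and address any violation of assumptions attributable to outliers".

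The section closes: "All tests of treatment effects will be conducted using a two-sided alpha level of 0.05 and 95% confidence intervals".

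Two other places matter. Random allocation stratifies by industry type, so that covariate is known before any data arrive. Primary outcome defines the endpoint as the level of PHQ-9 symptoms at 3 months.

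**The concern.** Under randomisation, a difference between arms in a baseline variable is chance. It does not show which variables predict the outcome; prior knowledge of prognosis does. A rule that admits variables on observed imbalance and then tests them against the outcome lets the trial's own data choose the primary model. The reported standard error is computed as if that model had been fixed.

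Two things are at stake: whether the primary test and interval have the error rate stated for them, and whether power is lost by leaving out prognostic variables that happen to be balanced. Industry type, used to stratify, has no stated place in the primary model and would enter only through this rule.

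The transformation sentence raises a smaller question of the same kind. If it reaches PHQ-9, the scale of the primary comparison also depends on inspection of the data, and a categorised score would no longer estimate a difference in symptom level.

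**Working it through.** The 5% level is a setting, not a derived figure, so there is nothing to reproduce. As a baseline check, models fixed in advance were simulated under no effect (266 per arm, score 0-27, pre-post correlation 0.50). They rejected in 4.5-5.4% of runs, which is nominal within Monte Carlo error.

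**Inputs from the document (Sample size).** 266 per group, 80% power, two-sided 0.05, 40% dropout, 851 recruited. Completers: 851 × 0.60 = 510.6, taken as n = 510. No numeric effect size is given. The one implied by 266 per group is d = (1.960 + 0.842) × √(2/266) = 0.243, in units of the SD the analysis uses.

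**Assumptions, not in the document.** Ten independent candidates beyond baseline PHQ-9, each explaining a share r of the variance (2% or 4%). Imbalance means an absolute standardised difference above 0.1. Flagged variables are retained. A single complete-data comparison stands in for the 3-month contrast of the mixed model.

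**Step 1: how often the rule acts.** The SD of a chance standardised difference is √(4/510) = 0.0886, and 0.1/0.0886 = 1.129. The probability of a flag is 2 × (1 − Φ(1.129)) = 0.259, or about 2.6 of ten. At least one is flagged with probability 1 − 0.741^10 = 0.95.

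**Step 2: what is left unadjusted.** An unflagged variable has its difference confined to ±0.1. The variance of that difference, as a fraction of the unrestricted one, is 1 − 2 × 1.129 × φ(1.129)/0.741 = 0.357.

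**Step 3: true against reported variance of the treatment estimate** (units of 4/n).
- True: A = 1 − 10r + 10 × 0.741 × 0.357 × r
- Reported: S = 1 − 10 × 0.259 × r
- Ratio of SDs: k = √(A/S)

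The reported variance still counts the full spread of the unflagged variables, although these contribute little to the difference between arms. That is why the test becomes conservative.

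**Step 4: error rate and power.** Type I error is 2 × (1 − Φ(1.96/k)). The noncentrality without covariates is 0.243 × √510/2 = 2.744. Power under the rule is Φ((2.744/√S − 1.96)/k). Power adjusting for all ten is Φ(2.744/√(1 − 10r) − 1.96).

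| r each | A | S | k | Type I, rule | Power, rule | Power, all ten fixed |
|---|---|---|---|---|---|---|
| 2% | 0.853 | 0.948 | 0.948 | 3.9% | 82% | 87% |
| 4% | 0.706 | 0.896 | 0.887 | 2.7% | 85% | 94% |

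With none of the ten in the model, power is Φ(2.744 − 1.96) = 78%.

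**Step 5: simulation with retention at p < 0.05.**
- r = 2%: type I error 3.7-4.5% under the rule; power 81%, against 85-86% with all ten fixed.
- r = 4%: type I error about 3.0%; power 85-86%, against 93-94%.
- Weak covariates (coefficients of 0.05-0.10 SD, so 0.25-1% of variance each): type I error 4.6-4.9%.
- Reading influence as a 10% change in the treatment estimate and filtering on that changes almost nothing.
- Reporting the better of the unadjusted and rule-adjusted results: 5.1-6.6% across settings.
- A square-root transformation triggered only by residual non-normality: 4.8-5.3%.

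**The case against.** The strongest reply is that the rule, followed as written, does not produce false positives. That stands: the calculation gives a level at or below 5%. A reader might infer from the wording that the 5% level is certainly broken upwards. The text does not support that. It asks for covariates that matter to the outcome; it does not ask for a choice among treatment estimates. Larger error rates can be produced by searching covariate subsets, scales or cut-points for the smallest p-value, but the article describes no such search. Nor does it say that whoever applies the rule sees the arm labels together with the treatment result.

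A second reply is that this is a condensed article, and that the candidate list, the imbalance threshold and the meaning of influence belong in an analysis plan. That also stands, and their absence is not the point. The point is the stated rule, which an analysis plan following the article would inherit.

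Third, power. A model restricted to baseline PHQ-9 and industry type could do worse than the rule: 78% against 81-86% here, if the ten candidates are further variables. This is correct and shapes the fix. The gain comes from naming prognostic variables in advance, not merely from deleting the rule.

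Fourth, the transformation sentence follows one about secondary measures, and sickness-absence counts are plausible targets. A reader might infer that PHQ-9 will be dichotomised. No cut-point is named, and Primary outcome speaks of symptom level. All that can be said is that the primary score is not clearly exempt.

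**Conclusion.** The concern holds in a limited form. The Analysis plan lets chance imbalance, then significance and influence, decide the primary model, so the stated level and coverage are not assured.

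Under ten assumed candidates explaining 2-4% each, mechanical use gives type I error of about 3-4.5%, which means intervals covering about 95.5-97%. Power is about 81-86%, against 86-94% for adjusting for the same variables in advance. With weak covariates the difference is negligible. Inflation to about 6% needs the more favourable of two results to be reported, which the text neither states nor excludes.

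These sizes depend on the assumed number and strength of covariates, the 0.1 threshold and an effect of 0.243 SD; the document gives none of them. The direction under mechanical use, conservative with some loss of power, does not depend on the exact values. The point should be fixed, but it does not undermine the trial.

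**What to change.** Delete the imbalance and significance rule. In its place state: 'The primary model includes baseline PHQ-9, industry type (the stratification factor) and the following prognostic baseline variables: [short list, named before arm-level data are seen]. All are kept whatever their imbalance or significance. Models adding other baseline variables are sensitivity analyses.'

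Add: 'The primary comparison of PHQ-9 at 3 months uses the raw 0-27 score. Any transformed or categorised version is a sensitivity analysis.'

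The cost is a few sentences and a decision on the list. The downside is that a chance imbalance in an unlisted variable is then handled only in a sensitivity analysis. With covariates and scale fixed in this way, the simulated type I error returns to 5% within Monte Carlo error.
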